### Outcome measures

Outcomes will be assessed at baseline and at 1-, 3-, 6-, and 12-month follow-ups. Outcome measures will be assessed by clinical research coordinator and summary of baseline screening, assessment, and follow-up during study visits is described in Table 2.

**Table 2 Tab2:** Summary of baseline screening, assessment, and follow-up during study visits

		STUDY PERIOD				
		Post-allocation				
TIMEPOINT		*Post op* *(± 1w)*	*1-month* *(± 2w)*	*3-month* *(± 1 m)*	*6-month* *(± 2 m)*	*12-month* *(± 2 m)*

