	**INTERVENTIONS**:					
	***Personalized digital therapeutic (intervention) group***					
	***Control group***					
	**ASSESSMENTS**:					
***7***	***Complication***		X	X	X	X
***8***	***Hb, albumin***	X ^1)^			X	X
***9***	***CT (visceral fat, muscle mass)***	X ^1)^			X	X
***10***	***Body composition***	X	X	X	X	X
***11***	***EORCT-QLQ-C30***	X	X	X	X	X
***12***	***EORCT-QLQ-CR29***	X	X	X	X	X
***13***	***MNA***	X	X	X	X	X
***14***	***IPAQ-SF***		X	X	X	X
***15***	***Grip strength***	X	X	X	X	X
***16***	***30 s chair stands test***		X	X	X	X
***17***	***2 min walk test***		X	X	X	X
***18***	^***a***^ ***LARS***		X	X	X	X
***19***	^***b***^ ***Satisfaction questionnaire***				X	

*CT*: computed tomography, *EORCT-QLQ*: European Organization for Research and Treatment of Cancer-Quality of life Questionnaire, *MNA*: Mini Nutritional Assessment, *IPAQ-SF*: International Physical Activity Questionnaire-Short Form, *LARS*: Low Anterior Resection Syndrome Score Questionnaire

^a^ Rectal cancer without ileostomy and colostomy.

^b^ Digital therapeutic group only.

^1)^ Tests analyzed within previous 6 months from the baseline can be collected.

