### Primary outcome

The primary objective of this study is to determine the effect of mobile application and wearable smart band in the management of prognostic factors in colorectal cancer patients. Therefore, the primary outcome would be the skeletal muscle mass increment in the intervention group compared to the control group in 12 months from the baseline, measured using the bio impedance analysis.

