### Secondary outcomes

The secondary objectives of our study are quality of life, body function and composition, and pain intensity over time.

The quality of life will be evaluated using the European Organization for Research and Treatment of Cancer-Quality of life Questionnaire (EORCT-QLQ-C30 and CR29). EORTC QLQ-C30 is composed of functional, symptom, and global quality of life domain. The quality-of-life scale uses a modified 7-point linear analog scale. All other items are scored on a 4-point categorical scale, ranging from 1 “not at all” to 4 “very much” [10]. The EORTC QLQ-CR29 is designed to complement the C30 questionnaire as a tumor-specific questionnaire for patients with colorectal cancer. It is composed of function and symptom domains [11, 12]. High overall quality-of-life, high functional domain score, and low symptom domain score correlates with high quality of life.

International physical activity questionnaire-short form (IPAQ-SF) is divided into vigorous activity, moderate activity, walking, and lying down to evaluate the amount of activity in the last seven days. The participants are also asked to define the number of min and days spent performing a specific activity category [13].

Mini nutritional assessment (MNA) defines nutritional status. It is divided into several domains for anthropometric assessment (weight, height, and weight and appetite loss) [14]. The total score is 30 points, < 17 points indicates malnutrition, 17–23.5 points indicate risk of malnutrition, and 24–30 points is considered normal.

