### Statistical analysis

All data will be analyzed using IBM SPSS Statistics version 28.0.1 (Armonk, New York, USA) and a significance level of 5% will be set with a 95% confidence interval. Patient demographics will be calculated using descriptive statistics. Kolmogorov–Smirnov test will be performed to assess the distribution of data. To compare baselines between the two groups, a student’s t-test and chi-squared test will be conducted. In case the randomization is not balanced, the baseline difference will be corrected through multivariate logistic regression and analyzed. To compare the mean difference, if the primary outcome (skeletal muscle mass) data in both groups are found to be normally distributed, we will perform an independent t-test. Missing data will be handled depending on the distribution of data after study completion. To investigate the effects of the interventions and differences between groups for secondary outcomes, a mixed effects model or generalized estimating equations will be conducted, with one between-subject factor (group) and one within-subject factor (evaluation time).

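### The secondary-outcome model names no baseline covariate and does not say which between-group difference is reported, although most continuous secondary outcomes are measured at baseline

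*Protocol article*

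**What the plan says.** In the protocol article, Statistical analysis, the aim of the secondary analysis is "To investigate the effects of the interventions and differences between groups for secondary outcomes". The method is that "a mixed effects model or generalized estimating equations will be conducted", "with one between-subject factor (group) and one within-subject factor (evaluation time"). The sentence does not mention a baseline covariate, a group-by-time term or a particular contrast.

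Under Outcome measures, "Outcomes will be assessed at baseline and at 1-, 3-, 6-, and 12-month follow-ups", so evaluation time includes baseline. In Table 2, QLQ-C30, CR29, MNA, grip strength and body composition have a value at the post-operative visit and at all four follow-ups. IPAQ-SF, the chair stand test, the 2-minute walk and LARS start at 1 month. The CT measures have baseline, 6 and 12 months.

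Statistical analysis has one sentence on baseline differences. Groups are compared at baseline by t-test and chi-squared test, and if they are not balanced the difference is corrected by multivariate logistic regression.

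On time frame, Secondary outcomes states that "The secondary objectives of our study are quality of life, body function and composition, and pain intensity over time". The 12-month comparison belongs to the primary outcome: "the skeletal muscle mass increment in the intervention group compared to the control group in 12 months from the baseline".

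**The concern.** Two features of the stated analysis work against the secondary outcomes.

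First, baseline is one of the evaluation times and nothing moves it out of the response. At baseline the expected group difference under randomization is zero. A result averaged over all visits would mix that zero with the treated visits.

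Second, baseline is not used as a covariate from the outset. Adjustment depends on an observed imbalance, so the final model depends on the data. The method named for it models a binary outcome, whereas quality-of-life scores, grip strength, weight and fat mass are continuous.

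At stake are the meaning and the precision of the secondary results. The primary t-test is not affected.

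**Working it through.** **Inputs from the protocol article.** Sample size calculation: effect size 0.35, power 80%, allocation 1:2, at least 195 intervention and 97 control, 10% drop-out, 324 in total. Statistical analysis: 5% significance level. Outcome measures and Table 2: visits at baseline, 1, 3, 6 and 12 months.

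**Assumptions, not in the document.** True 12-month difference 0.35 SD (the sample-size effect, borrowed for illustration); equal SD at each visit; compound symmetry with within-patient correlation ρ of 0.5 to 0.8; complete data on 195/97; the time courses below.

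**Step 1. The plan's own figure.** A two-sided 5% t-test at 0.35 SD and 80% power needs 97 and 194 patients. At 97 and 195, power is 80.2%. With drop-out, 292/0.9 = 324.4, against 324 stated. The figure reproduces, and the point does not depend on it.

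**Step 2. If only the group main effect were reported, with baseline in the response.** With balanced data, the group coefficient is the mean of the visit-specific differences. Relative to the 12-month difference:

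| Assumed effect at 0, 1, 3, 6, 12 months | Five visits (with baseline) | Four visits (no baseline value) |
|---|---|---|
| Proportional to time: 0, 1/12, 3/12, 6/12, 1 | 1.833/5 = 0.37 | 1.833/4 = 0.46 |
| Even steps: 0, 0.25, 0.5, 0.75, 1 | 2.5/5 = 0.50 | 2.5/4 = 0.625 |
| Constant from month 1: 0, 1, 1, 1, 1 | 4/5 = 0.80 | 4/4 = 1.00 |
| Early, halved by month 12: 0, 1, 1, 0.75, 0.5 | (3.25/5)/0.5 = 1.30 | (3.25/4)/0.5 = 1.63 |

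A GEE fit to simulated data (20 × 324 = 6,480 patients, even steps, ρ = 0.6, true 12-month difference 0.35) gave 0.18 for the main-effects coefficient. With group-by-time included, it gave 0.34 at 12 months.

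**Step 3. If group-by-time is included.** The 12-month difference can then be estimated, so the question is precision. Let c = 1/195 + 1/97 = 0.01544, with SD 1. The variances are:

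- 12-month difference, baseline not used: c
- difference in change from baseline: 2(1 − ρ)c
- 12-month difference with baseline as covariate: (1 − ρ²)c

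The last divided by the second is (1 + ρ)/2. This is 0.75 at ρ = 0.5 and 0.90 at ρ = 0.8, so variance falls by 25% and 10%. Against the difference that does not use baseline, the fall is ρ², or 25% and 64%.

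Power at 0.35 SD, two-sided 5%:

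| ρ | Baseline not used | Change from baseline | Baseline as covariate |
|---|---|---|---|
| 0.5 | 80% | 80% | 90% |
| 0.7 | 80% | 95% | 98% |
| 0.8 | 80% | 99.4% | 99.7% |

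At ρ = 0.5 with baseline as covariate: 0.35/√(0.75 × 0.01544) = 3.25, and 3.25 − 1.96 = 1.29, giving power of 90%.

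**The case against.** A reader might infer that the model is fixed as main effects only, so that the plan is bound to understate the 12-month effect. The document does not support this, for four reasons.

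- Naming one between-subject and one within-subject factor is ordinary wording for a two-factor repeated-measures layout, in which the interaction is normally examined. The text neither includes nor excludes it, and does not name the group main effect as the reported result.
- No 12-month target is set for the secondary outcomes, whose objectives are stated as over time.
- Four instruments have no baseline value in Table 2, so there is no baseline zero to average in.
- The direction depends on the time course. Under Interventions, usage feedback is given only in the first 3 months, so an early effect that fades cannot be dismissed, and averaging would overstate it.

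All of this stands. It is also fair that an article may leave interaction terms and contrasts to a fuller document, so their absence alone is no finding. With the interaction in the model, low power is not the main issue either: under the same assumptions the 4-df omnibus interaction test has 71% to over 99% power, though it gives no effect size by itself.

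The objection does not remove what the article does state. Baseline is an evaluation time, and the only baseline correction described is conditional on observed imbalance and uses a method for binary outcomes.

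**Conclusion.** The point holds as a free improvement, not as a demonstrated bias. On either reading of the model sentence, baseline values already collected are not put to their best use, and the reported between-group quantity is left open.

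If the interaction is fitted, the loss is one of precision: 10% to 25% of the variance against change from baseline, and 25% to 64% against a difference that does not use baseline, for ρ from 0.8 down to 0.5 in the first case and from 0.5 up to 0.8 in the second. If only the group main effect were reported, the misstatement for outcomes with five visits would range from 37% to 130% of the 12-month difference over the time courses tried.

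These sizes rest on assumed correlations, time courses and effect size, since the document gives none of them for any secondary outcome. The absence of a baseline covariate and the conditional logistic correction are in the text and need no assumption.

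**What to change.** Replace the model sentence with a prespecified one:

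- **Continuous secondary outcomes with a baseline value** (QLQ-C30 and CR29, MNA, grip strength, weight, fat mass): model the 1-, 3-, 6- and 12-month values, with the baseline value as covariate and group, visit and group-by-visit as fixed effects.
- **Outcomes first measured at 1 month** (IPAQ-SF, chair stand, 2-minute walk, LARS): the same model without the baseline covariate.
- **Reporting:** between-group differences at each visit with 95% CIs, including 12 months. Including 12 months matches the primary outcome; it is a recommendation, not something the document requires.
- **Baseline correction:** for these outcomes, drop the logistic-regression correction that is triggered by observed imbalance. The covariate takes its place.

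Either the mixed model or GEE may be kept. If the interaction was always intended, stating it settles that part.

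The cost is wording and a few more model parameters. No extra data are needed, and the models can be fitted in the software already named.

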**Methods:**

This study is a prospective, multi-center, single-blinded, two-armed, randomized controlled trial. The study aims to recruit 324 patients from three hospitals. Patients will be randomly allocated to two groups for one year of rehabilitation, starting immediately after the operation: a digital healthcare system rehabilitation (intervention) group and a conventional education-based rehabilitation (control) group. The primary objective of this protocol is to clarify the effect of digital healthcare system rehabilitation on skeletal muscle mass increment in patients with colorectal cancer. The secondary outcomes would be the improvement in quality of life measured by EORTC QLQ C30 and CR29, enhanced physical fitness level measured by grip strength test, 30-sec chair stand test and 2-min walk test, increased physical activity measured by IPAQ-SF, alleviated pain intensity, decreased severity of the LARS, weight, and fat mass. These measurements will be held on enrollment and at 1, 3, 6 and 12 months thereafter.

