### Participants

In this study, we will enroll 324 participants who were diagnosed with colorectal cancer and have undergone surgery. The inclusion criteria will be as follows: (a) aged 19–85 years, (b) diagnosed with colorectal cancer and undergone colorectal cancer resection surgery, (c) uses an Android- or iOS-based smartphone, (d) able to use mobile application and have regular follow-up assessment as outpatient, (e) voluntary participation. The exclusion criteria will be as follows: (a) unable to perform exercise and diet management because of severe underlying disease, neuromusculoskeletal disease, or cognitive or visual impairment, (b) communication difficulties.

All eligible patients will be informed about this study, and after consultation with the department of surgery and the department of rehabilitation medicine they will be invited to participate. All patients will submit a written informed consent if they agree to participate in the study.

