	**ENROLLMENT**:					
***1***	***Eligibility screening***	X				
***2***	***Informed consent***	X				
	***Allocation***	X				
***3***	***Demographic characteristic***	X				
***4***	***Medical history***	X				
***5***	***Health lifestyle***	X				
***6***	^***b***^ ***eHealth Literacy Scale***	X				

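### If Table 2 stands, chair stand, 2-minute walk, IPAQ-SF and LARS have no baseline value, and the stated model compares them without a prognostic covariate: unbiased, but less precise than it need be

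*Protocol article*

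**What the plan says.** **Model.** The Statistical analysis section gives one model for all secondary outcomes, a mixed effects model or generalized estimating equations, "with one between-subject factor (group) and one within-subject factor (evaluation time". It lists no covariate.

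**Adjustment clause.** The same section first compares the arms at baseline by t-test and chi-squared test. If they are not balanced, it would correct the difference by logistic regression.

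**Schedule.** In Table 2 the rows "30 s chair stands test", "2 min walk test", IPAQ-SF and LARS have an empty post-operative cell and are marked from 1 month on. LARS is further limited by a footnote: "Rectal cancer without ileostomy and colostomy". By contrast, "Grip strength" is marked at the post-operative visit and at all four follow-ups, and "Demographic characteristic" is recorded at enrolment. The Abstract and the opening of Outcome measures place outcome assessments at enrolment or baseline as well as at follow-up, with no exception for these four.

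**Population and timing.** Patients are "aged 19–85 years", with no restriction by sex. The Randomization, allocation, and blinding section describes an open study in which baseline assessment follows allocation.

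**The concern.** For quality of life, MNA, body composition and grip strength, Table 2 provides a baseline value that a repeated-measures model can use. For the other four it does not. Adding a group-by-time term, or adjusting other outcomes for their own baseline, would not help these four. As stated, their analysis is a plain comparison of follow-up values across a 66-year age range (85 − 19) in both sexes.

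The outcomes matter to the trial's secondary claims. The Abstract lists "enhanced physical fitness level measured by grip strength test, 30-sec chair stand test and 2-min walk test", and two of those three tests are affected. So is IPAQ-SF, the instrument the Abstract names for physical activity. Age is known for every patient and sex almost certainly is. If they predict performance, leaving them out widens the confidence intervals, and a real gain in fitness or activity is somewhat more likely to be missed.

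**Working it through.** **1. The plan's own figure.** The Sample size calculation section gives a standardised effect of 0.35, 80% power, 1:2 allocation, and 97 control and 195 intervention patients. A two-sample t-test at 5%, taken as two-sided because the protocol does not say, has power 80.2% at 97/195. The stated numbers therefore reproduce. The protocol states no power or precision target for the four outcomes discussed here, so this calculation supplies only the patient count, 97 + 195 = 292.

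**2. Which outcomes can use their own baseline (Table 2).**

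| Outcome | Post-operative value | Follow-up |
|---|---|---|
| Grip strength | yes | 1, 3, 6, 12 months |
| Chair stand | no | 1, 3, 6, 12 months |
| 2-minute walk | no | 1, 3, 6, 12 months |
| IPAQ-SF | no | 1, 3, 6, 12 months |
| LARS (subset) | no | 1, 3, 6, 12 months |

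**3. Which covariates are usable.** Age and sex cannot be altered by knowledge of the allocation. Age is certain to be held, since it is an eligibility criterion. Sex is assumed to be among the demographics, because the items are not listed. Baseline grip strength depends on the patient's effort and, as written, is measured after an open allocation. It is therefore not a safe covariate under the current schedule.

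**4. Effect on precision.** For a continuous outcome at one visit, let R² be the share of its variance that the covariates explain.

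- Standard error ratio, adjusted to unadjusted: √(1 − R²)
- Equivalent gain in patients: 1/(1 − R²) − 1

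The documents give no R². The values below are assumptions for age and sex alone.

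| Assumed R² | SE ratio | Fall in SE | Equivalent gain | 292 patients are worth |
|---|---|---|---|---|
| 0 | 1.000 | 0% | 0% | 292 |
| 0.05 | √0.95 = 0.975 | 2.5% | 1/0.95 − 1 = 5% | 292/0.95 = 307 |
| 0.10 | √0.90 = 0.949 | 5.1% | 1/0.90 − 1 = 11% | 292/0.90 = 324 |

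A simulation of one follow-up visit with 97 and 195 patients (4,000 runs) gave a standard error ratio of 0.952 at R² = 0.10, against 0.949 by formula.

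**5. Where this does not carry over.** LARS is scored only in rectal cancer patients without a stoma, so 292 is not its sample. If it is analysed by category, the √(1 − R²) rule does not apply directly. For IPAQ-SF the gain may be small. It is most plausible for chair stand and 2-minute walk.

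**The case against.** **The article need not list every covariate.** A full protocol or analysis plan may hold more, and the quoted phrase can be read as describing the repeated-measures layout rather than excluding covariates. That is fair, and it is why this is offered as an improvement. But the section does state the factors of the model, so the point concerns a stated choice and not a silence.

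**The unadjusted comparison is valid.** This stands in full. A reader might infer that the group effects for these outcomes are biased, or that chance differences in age or sex invalidate them. The documents do not support that: under randomisation such differences are part of the sampling error that the confidence interval already reflects.

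**The protocol already provides for imbalance.** It does, but the clause is triggered by looking at the data, names a model for binary outcomes, and does nothing for precision when the arms look alike. It does not settle the point.

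**The schedule is contradictory.** If the Abstract and Outcome measures text is right and a baseline is taken, own-baseline adjustment becomes available and most of the argument disappears. The point is therefore conditional on Table 2.

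**A larger gain is tempting.** At R² = 0.30 the formula gives a 16% fall in standard error, and power at d = 0.35 would rise from 80% to 92%. The documents support neither figure. That range was assumed for age, sex and grip strength together, and grip strength drops out while baseline follows open allocation. The effect size of 0.35 was not set for these outcomes.

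**Conclusion.** The point holds as a free improvement, provided Table 2 is the correct schedule. The stated comparison of the four outcomes is unbiased but leaves available prognostic information unused. The illustrated size is a 2.5% to 5% smaller standard error, equivalent to 5% to 11% more patients. It rests on an assumed R² of 0.05 to 0.10 and applies to a continuous outcome measured in all patients. No gain is claimed if R² is near zero, and no figure is claimed for LARS.

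**What to change.** 1. Reconcile Table 2 with the Abstract and Outcome measures text on whether these four outcomes have a baseline assessment.
2. If Table 2 stands, add one sentence to the Statistical analysis section: the models for chair stand, 2-minute walk, IPAQ-SF and LARS include age and sex as fixed covariates, whatever the observed balance. Confirm that sex is among the demographics collected.
3. For chair stand and 2-minute walk only, add baseline grip strength if it is measured before allocation is disclosed. The protocol does not currently provide for this; unless that changes, use age and sex alone.

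The cost is that sentence, with no new patient, visit or measurement. The one constraint is that the covariates must be fixed before outcome data are examined. If grip strength is used, a rule for missing baseline values is also needed.

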## Discussion

Owing to COVID-19 pandemic, home-based exercise is emerging as a promising tool for physical therapy. However, the biggest shortcoming of home-based program is still the poor management of compliance. Contrarily, previous studies on health management service applications had segmental interventions, such as only applying the health program during chemotherapy or dealing mainly with only psychological or nutrition-related issues [25, 26]. Most of them enrolled a small number of patients; insufficient to apply to general population. Although, studies regarding digital health issues are increasing in number, cancer related issues have not been addressed yet. Until now, adequate home-based exercise program with digital health platform that patients with colorectal cancer can use has been lacking, especially for the patients not eligible for regular visit to outpatient clinic. Therefore, for the sake of such patients, a comprehensive multimodal personalized digital intervention with easy-to-access mobile app is necessary, which manages hardships in every postoperative phase and enhances the patients’ physical activity and nutrition right after the operation. Consequently, a good quality of life, enhanced physical activity, and an easy return-to-society can be achieved, by managing the health behavior and nutrition status of the patients.

To the best of our knowledge, this will be the first randomized clinical trial performing digital therapeutics for personalized postoperative rehabilitation in patients with colorectal cancer. The study has several differentiated strong points. First, it starts immediately after the operation for one year. Second, a large number of colorectal cancer patients will be enrolled. Third, the program will be composed of a tailored digital health intervention, modified according to the treatment phase and patient condition. Another short-term positive consequence of our program includes reduction of financial and time burden on patients as well as on clinicians. In the long term, an integrated medical management of disease and psychological intervention would enable more comprehensive disease controlling systems.

In conclusion, this study will clarify the effect of patient-centered mobile and wearable digital health interventions on immediate postoperative rehabilitation of the patients with colorectal cancer. The study will add foundations for the application of comprehensive digital healthcare programs in postoperative rehabilitation for cancer patients in remote areas.

